## Abstract

**Background:**

Integration of physical activity (PA) into the classroom may be an effective way of promoting the learning and academic achievement of children at elementary school. This paper describes the research design and methodology of an intervention study examining the effect of classroom-based PA on mathematical achievement, creativity, executive function, body mass index and aerobic fitness.

**Methods:**

The study was designed as a school-based cluster-randomized controlled trial targeting schoolchildren in 1st grade, and was carried out between August 2012 and June 2013. Eligible schools in two municipalities in the Region of Southern Denmark were invited to participate in the study. After stratification by municipality, twelve schools were randomized to either an intervention group or a control group, comprising a total of 505 children with mean age 7.2 ± 0.3 years. The intervention was a 9-month classroom-based PA program that involved integration of PA into the math lessons delivered by the schools’ math teachers. The primary study outcome was change in math achievement, measured by a 45-minute standardized math test. Secondary outcomes were change in executive function (using a modified Eriksen flanker task and the Behavior Rating Inventory of Executive Function (BRIEF) questionnaire filled out by the parents), creativity (using the Torrance Tests of Creative Thinking, TTCT), aerobic fitness (by the Andersen intermittent shuttle-run test) and body mass index. PA during math lessons and total PA (including time spent outside school) were assessed using accelerometry. Math teachers used Short Message Service (SMS)-tracking to report on compliance with the PA intervention and on their motivation for implementing PA in math lessons. Parents used SMS-tracking to register their children’s PA behavior in leisure time.

**Discussion:**

The results of this randomized controlled trial are expected to provide schools and policy-makers with significant new insights into the potential of classroom-based PA to improve cognition and academic achievement in children.

**Trial registration:**

Clinicaltrials.gov: NCT02488460 (06/29/2015)

## Background

Physical activity (PA) in schools has historically received little attention and, in many countries, economic concerns and a greater focus on standardized testing have reduced the time spent on physical activity in favor of academic classes [1–4]. A regular school day often includes very little PA and children are required to sit quietly in the same position for long periods of time [5–7]. However, this may not be the most effective way of enhancing children’s academic achievement. Breaking up the sitting periods with physical activity might be a better approach to promote learning [8, 9].

PA has several cognitive and physiological benefits [10, 11]. A meta-analysis showed a significant positive relationship between PA in general and cognition in children [12]. This is consistent with the “executive function hypothesis”, in which PA is believed to enhance executive functions that are crucial to the learning process, such as organization and integration of information, and modulation of behavior through selective attention (e.g. [13–16]). Studies report clear acute cognitive benefits of PA, typically increased information processing speed or response accuracy [17–19]. Early experiments on the effects of regular PA showed either no effect of PA on cognitive outcomes [20] or limited improvements [21, 22]. However, recent studies report positive effects of regular PA on the structures and functions of the brain [14, 23–25]. Possible neurophysiological mechanisms of PA include changes in brain blood flow and arousal level, improved conduction of information due to increased concentration of neurotransmitters and receptors, as well as increased concentrations of growth factors important for the development of new brain cells [26]. In addition, regular PA may increase brain volume (e.g. the volume of the anterior hippocampus), leading to improved spatial and relational memory [14, 27, 28]. Lastly, a recent study demonstrated a positive relation between mathematic achievement and decreased gray matter thickness in the superior frontal cortex, superior temporal areas, and lateral occipital cortex, in more fit children [29]. This suggests that aerobic fitness is essential for the normal thinning of the cortical gray matter during brain maturation, thus providing us with a predictor of math performance that could in turn help educators to identify interventions that can enhance learning.

Despite the increasing evidence for an association between PA or fitness and cognitive performance [30–35], few high-quality longitudinal studies have examined the effect of PA on academic performance (rather than cognitive control or other educational outcomes) [8, 14]. Furthermore, to the best of our knowledge, only three studies have assessed academic outcomes following the integration of PA into the classroom. A study conducted among US elementary school children reported that children with 90 min/week of moderate to vigorous physical activity in academic lessons over three years showed greater academic improvement than controls [36]. However, these results were considered secondary and were based on a small subsample (*n* = 203) of the study. Another small-scale randomized experiment from the US conducted among 3rd grade children showed that integrating 30 min of PA three days per week for three months gave mixed results for academic improvement compared with controls [37]. Finally, a recent study showed that physically active academic lessons significantly improved mathematics and spelling performance of elementary school children [38].

Even the studies investigating the link between PA and cognition have typically examined cognition and PA separately, possibly due to a commonly held view that the mind and body function separately. However, recent theories of embodied cognition have emerged in several disciplines to challenge this traditional dualistic approach [39–46]. These theories consider the body to be a key factor in shaping our cognition, where ‘non-cognitive’ processes of acting and perceiving providing bodily experience are fundamental to and inseparable from the development of important cognitive functions. This emphasizes the importance of sensory–motor interactions with our environment during learning, resulting in more endurable and richer consolidation of knowledge [47]. This psychological and neuroscientific research has implications for education as it emphasizes the importance of suitable sensory and motor interactions during learning for the development of human cognition [47]. 

We designed a randomized controlled trial with the primary aim of investigating the effect on mathematical achievement of incorporating physical activity in math teaching for 7-year-old schoolchildren. Secondary aims of the study were to investigate effects on executive function, and the longitudinal associations between PA and creativity, math, executive function, body mass index and aerobic fitness. The hypothesis was that PA integrated into classroom teaching would be superior to traditional, physically inactive classroom teaching in facilitating learning, and would be associated with a greater improvement in academic skills.

## Methods

### Study design

The study was designed as a cluster-randomized controlled trial with two arms. In two municipalities in the southern part of Denmark, twelve elementary schools were randomized to either active math intervention (*n* = 7) or control (*n* = 5) (Fig. 1). Randomization was performed by random selection of sealed envelopes containing the intervention allocation stratified by municipality, in the presence of school leaders, municipality representatives and study researchers.

**Fig. 1 Fig1:**
[figure not shown]
Flowchart of recruitment and randomization of schools in the study

### Recruitment of participants

We approached three municipalities in the Region of Southern Denmark with the aim of recruiting schools and 1st grade children to the study. One municipality (15 schools) declined to participate. We hypothesized that children in this age group would particularly benefit from a classroom-based PA intervention, as they were likely to be struggling to sit in the same position in lessons for the majority of the day. Schools in these municipalities were eligible if they did not have a structured program that incorporated PA in the classroom.

Out of the 48 eligible schools that were invited to participate in the study, 12 schools accepted (7 in Svendborg municipality and 5 in Kolding municipality). The 1st grade children in these schools were invited to participate in a letter describing the study, measurement methods, randomization procedure and consent form. The children, parents and teachers were then invited to a meeting at the school, where a full description of the scientific background and the study was given. After this, 90.7 % of parents gave consent for their child to participate in the study, corresponding to 505 out of 557 students in 26 different classes. The excluded children received the same intervention as their classmates but did not participate in testing. A flowchart illustrating the recruitment and randomization process is shown in Fig. 1.

In Svendborg municipality, the participating schools were all part of an existing intervention study that had been initiated in 2008 (the CHAMPS-study DK). This intervention consisted of four extra lessons of physical education (PE) each week, in addition to the two compulsory lessons, resulting in a total of 4.5 h extra per week, divided over at least three weekly sessions of at least 60 min (a more detailed description of the CHAMPS-study DK can be found in [48]). To ensure that the extra PE lessons in Svendborg municipality did not bias the results of the present study, randomization to the intervention was stratified by municipality.

All schools were co-educational schools, with gender integrated classes in all subjects, which is typical for the Danish educational system.

Written parental consent was requested from parents in the included schools. Exclusion criteria were physical disability or no written parental consent. The trial protocol was approved by the ethics committee of the Region of Southern Denmark (S-20140105) and registered at clinicaltrials.gov (NCT02488460).

## The classroom-based PA intervention

The active math intervention consisted of math teaching that implemented PA in the classroom as a facilitating instrument. The intervention period lasted one school year, during which the students received on average 6 math lessons of 45 min per week with physically active teaching. PA in this math intervention was defined as any bodily movement produced by skeletal muscles that resulted in increased energy expenditure [49]. This is similar to the definition known as movement integration (MI) [50].

Each 45-minute lesson consisted of at least 15 min of PA spread over the lesson. Math lessons usually took place in the classroom, but were also held in other school areas such as corridors and surrounding outdoor areas. Sedentary activities were limited to periods of maximum 20 min, given that most students are unable to sustain attention on one thing for more than about 20 min at a time [51]. The rationale behind the active math was that if an abstract phenomenon is connected to a concrete bodily experience other than just seeing or hearing it, the comprehension and memory of the given phenomenon could be optimized (e.g. [52, 53]). In addition, we expected that breaking up the cognitive load imposed by a learning task would limit overload of working memory in the children and thus help maintain focus [54]. Studies have detected limited working memory capacity in children, and spreading the load across different working memory subsystems might prevent overload in one specific subsystem [55–57]. The active math lessons followed the principles of “learning by doing” and the development of practical life skills that are crucial to children’s education [58]. This is related to experiential learning theory, i.e. learning through action and experience as opposed to through repetition [59, 60]. The active math approach was adopted for all math lessons for the entire school year. Appendix 1 provides examples from the active math intervention.

Children in the control schools received regular classroom instruction, also with an average of 6 math lessons of 45 min per week. The math teachers in the control schools were asked not to make any changes to their usual teaching methods before the study endpoint measurements. This was accepted with the agreement that at the end of the study, these teachers would receive the same training in physically active math teaching as the teachers in the intervention group.

### Teacher training for the intervention

Teachers in the intervention schools attended a 4-day mandatory course on how to integrate active math into the Danish curriculum for mathematics in public schools. The aim of the course was to provide the teachers with the skills to implement physically active math lessons, i.e. to use suggested methods and develop new ways of integrating physical activity into lessons, to organize the activities and to report on intensity of PA (for an overview of the course plan, see Appendix 2).

The research group developed the training course and the associated training material that included specific instructions and inspiration for how teachers could integrate PA as an element of academic instruction in math lessons. Examples from this material were used to help illustrate the practical dimensions of the active math lessons. It should be noted that the focus of the course was on developing the teacher’s own abilities to design active math lessons and thus their own pedagogical skills and knowledge rather than handing out a complete manual with activities for the math lessons. The course included an introduction to the study context and aims, with emphasis on creating high motivation among the teachers for the intervention by explaining the numerous potential positive cognitive effects of learning through action and describing previous findings related to PA in general. The teacher’s motivation for implementing PA in the classroom and their involvement are highly relevant matters for math achievement [61], and could influence the outcome of the study. The teachers thus played an active role in creating and developing the activities for the math lessons. Furthermore, several theories of how to develop activities in the classroom were presented e.g. the ‘Activity-wheel’ [62], with the purpose of creating activities that would help the children to reach the desired learning objectives.

On the last course day, active teaching techniques were discussed and related to motivational, organizational and management techniques. Several teachers attending the course highlighted the challenges they expected to face when implementing PA in math. This initiated an internet-based intra-school communication forum in each of the two municipalities, where the teachers shared activities, experiences and advice for the active math intervention. The teachers received normal salary for attending the course, as compensation for their time.

## Baseline and follow-up assessments

The study was carried out over nine months from August 2012 to May/June 2013. Unfortunately during this period, all Danish schools were closed for a month due to a teacher lockout as a result of a union-employer dispute. Thus in the final period of the intervention, participants did not attend school for 25 days during April/May 2013. This period ended 4 weeks prior to the end of the intervention.

The test battery included measurements of math skills, cognitive function, creativity, aerobic fitness, anthropometrics and level of PA. Prior to testing, the research assistants (i.e. master’s and PhD students) were thoroughly trained in conduction of the test battery to ensure valid and uniform data collection. The training included several test trials with feedback and was performed at the University of Southern Denmark by a researcher experienced in the techniques. The research assistants were blinded to the randomization result for measurement of the outcomes and for data entry. All tests were performed at the participating schools either in the classrooms or a gym, except for the assessment of executive function (Flanker task), which was performed in smaller rooms with a maximum of two students present at the same time. Each outcome measure was assessed at baseline and follow-up using the methods described below. The tests applied at baseline and follow-up were identical.

### Mathematical skills test

Math skills were evaluated using a 45-minute standardized math test (MG) that was specifically designed for this age group by the developer of the Danish national tests (Hoegrefe Forlag) [63]. It consisted of 24 tasks assessing calculus and math in terms of the understanding of quantity and numbers, relations, addition, subtraction and geometry, with the final score ranging between 0 and 24. MG is a common test material in Danish primary schools and has been used for more than 25 years [63]. It is based on multiple-choice questions, and the different response options were selected in such a way that incorrect options related to typical mistakes made by students in 1st grade. The test provides a score reflecting the participant’s math skills and was conducted individually with paper and pencil in a classroom, with no aids permitted. Following a general presentation of the test, the participants were presented with each task separately and given 1 min to answer. The number of correct answers was used for further analysis.

### Flanker test

Executive functions were identified as working memory, inhibition, and cognitive flexibility, which were evaluated using a computer-based modified Erickson Flanker task [64]. Modified versions of the Flanker task have been used in previous studies indicating that the test is sensitive enough to detect changes in cognitive function associated with exercise [65]. The tests were conducted with the child seated at a 15” laptop with an external keyboard on which the corner keys with right and left arrows were clearly marked.

The task was to focus on a target stimulus ignoring other distracting stimuli. In this version, the stimuli were pictograms of fish, and the child was instructed to “feed” the fish by pressing the arrow in the direction the target stimulus (fish) was facing (Fig. 2). The test consisted of three conditions: (a) standard flanker, (b) reverse flanker, and (c) mixed trials. In the standard flanker condition, fish were blue and subjects were instructed to press the arrow that pointed in the direction the middle fish was facing (target stimulus), ignoring the distractor fish on either side. This task required remembering the rule for the task, paying attention to the task, and inhibiting distraction from the flanker fish on either side of the target stimulus. In the reverse flanker condition, the fish were pink. In contrast to the previous task, the child was now instructed to press the arrow that pointed in the direction the fish on either side (target stimulus) of the central fish were facing. Not only did this task require remembering the new rule for the task and selective attention, it also required cognitive flexibility to change from the strategy used for the standard flanker task. In the third condition of mixed trials, standard flanker (blue fish) and reverse flanker (pink fish) tasks were randomly intermingled, requiring flexible application of the rules for each task. This made a heavy demand on all three core executive functions and was expected to detect small individual and group differences.

**Fig. 2 Fig2:**
[figure not shown]
Stimuli in Flanker test for executive function. Examples of the four types of stimulus in the standard flanker (target stimulus: middle fish) and reverse flanker (target stimulus: ‘non-middle’ fish) conditions respectively

The child was thoroughly instructed in the test by one of the research assistants, and made two familiarization rounds with blue and pink fish to ensure understanding of the task. Familiarization rounds consisted of four ‘habituation tasks’ where the child received verbal feedback from the test administrator, and then 17 further tasks. The child was instructed to respond as quickly and as accurately as possibly by pressing the left or right arrow on the keyboard. Each task was shown on the screen until an answer was given.

The test itself consisted of 45 tasks, with the first one not included in the analysis to exclude possible delay in the start-up. To test the child’s ability to focus and exclude interfering stimuli, the flankers were divided into four categories: 1) ‘congruent’ stimuli in which the flanking stimuli were identical to the target stimulus, 2) ‘incongruent’ stimuli in which the flanking stimuli were the opposite of the target stimulus, 3) ‘No distractors’ with no flanking stimuli and 4) ‘Neutrals’ in which the flanking stimuli were neither identical nor opposite of the primary stimuli but were vertically placed. The 44 tasks were divided equally between flanker conditions and contained 12 congruent, 16 incongruent, 8 no-distracter and 8 neutral tasks. These were also evenly divided between right and left as the correct answer. The stimulus presentation time was 1500 ms, the feedback interval was 1000 ms, and the interstimulus interval was 500 ms. The response time of the different tasks were recorded and the following variables were calculated: i) % accurate congruent answers, ii) % accurate incongruent answers, iii) the reaction time for correct congruent answers, and iv) the reaction time for correct incongruent answers. These parameters have previously been related to high levels of physical activity and fitness [66].

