## Discussion

The literature lacks well-designed large-scaled randomized controlled trials on the effect of classroom-based physical activity on academic achievement and cognition. The present study will contribute to the field by generating detailed knowledge about the relationship between physical experiences that are combined with abstract math information and the acquisition of math skills. We expect the study results to provide schools and education policy-makers with an evidence base for implementing physical activity in daily school life, as a change from schoolchildren sitting still much of the day.

Apart from the large sample size and the comprehensive follow-up of children’s learning experiences and physical behavior over nine months, this study includes detailed measurement of the primary and secondary outcomes using well-validated methods. The math test applied in this study has been used for over 25 years to assess the math skills of Danish schoolchildren. The complex flanker task that assesses the three core executive functions will allow us to verify the few previous research findings concerning the association between a change in physical activity level and the ability to focus on a target stimulus and inhibit distractions [14, 74]. Furthermore, we expect the combination of SMS-tracking and accelerometry to be an excellent solution for measuring physical activity in large cohort studies. This makes it possible to compensate for some of the problems associated with accelerometry measurements, for example by using SMS-tracking to ask questions about specific activities, including water activities, and to allow more precise measurement of exercise intensity during cycling. When all this information is coupled to the class school timetable, then we can analyze the physical activity undertaken in specific time periods such as lunch breaks or during the math lessons. However, accelerometry does not provide any qualitative detail about the types or modes of activity being undertaken. For this reason accelerometry measurements were combined with video recordings of math lessons.

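### The four listed Flanker variables give no separate measure of cognitive flexibility or working memory and omit the interference contrast needed for inhibition, although the task is said to assess all three

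*Protocol article*

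**What the plan says.** In the protocol article, the Flanker test section opens with the claim: "Executive functions were identified as working memory, inhibition, and cognitive flexibility, which were evaluated using a computer-based modified Erickson Flanker task". The Discussion repeats it, referring to "The complex flanker task that assesses the three core executive functions", and adds that the task will bear on the ability to focus on a target and resist distraction.

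The same section describes the layout: "The test consisted of three conditions: (a) standard flanker, (b) reverse flanker, and (c) mixed trials". It ties flexibility to the change of rule in the reverse condition and to moving between rules in the mixed one. Of the latter it says: "In the third condition of mixed trials, standard flanker (blue fish) and reverse flanker (pink fish) tasks were randomly intermingled".

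The text under the Fig. 2 caption gives the scored test: 45 tasks, of which the first is dropped. It continues: "The 44 tasks were divided equally between flanker conditions and contained 12 congruent, 16 incongruent, 8 no-distracter and 8 neutral tasks". Correct answers are also balanced between left and right. The outcomes are then listed: "the following variables were calculated: i) % accurate congruent answers, ii) % accurate incongruent answers", followed by reaction time for correct congruent and for correct incongruent answers. No other Flanker variable is named.

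**The concern.** The claim covers three functions, but the list of variables is organised by one feature only, the stimulus type. The feature that the article itself links to flexibility, the rule in force and the change between rules, does not appear in any listed variable. Working memory has no variable of its own either.

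For inhibition, the ingredients are listed but the contrast is not. Congruent tasks carry no conflicting distractor, so performance on them mostly reflects speed, attention and understanding of the task. Performance on incongruent tasks reflects all of that plus the cost of conflict. A between-arm difference in either raw variable therefore does not show that inhibition changed.

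The effect on executive function is a stated secondary aim. A general gain in response speed could be read as an executive-function effect. A change confined to rule switching could go unseen, because the listed variables pool over it.

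**Working it through.** **1. Task count.** Inputs, from the text under the Fig. 2 caption: 45 tasks given, first one dropped; 12 congruent, 16 incongruent, 8 no-distracter, 8 neutral.

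45 − 1 = 44, and 12 + 16 + 8 + 8 = 44. The stated total reproduces.

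**2. Equal division between flanker conditions.** Each count is divided by the number of conditions k. For k = 2 it is divided again by the two response sides.

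| | Total | k = 3 | k = 2 | k = 2, per side |
|---|---|---|---|---|
| Congruent | 12 | 4 | 6 | 3 |
| Incongruent | 16 | 5.33 | 8 | 4 |
| No distracter | 8 | 2.67 | 4 | 2 |
| Neutral | 8 | 2.67 | 4 | 2 |
| All | 44 | 14.67 | 22 | 11 |

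Three conditions do not divide equally. Two do, and every stated balance then holds in whole numbers.

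**3. What each listed variable can show.**

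| Function claimed | Contrast that would address it | Listed? | Derivable from the four variables? |
|---|---|---|---|
| Inhibition | Incongruent minus congruent | No | Yes, per child |
| Flexibility | Reverse versus standard, or switch versus repeat, depending on task order | No | No; needs task-level responses |
| Working memory | None described | No | No |

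The no-distracter and neutral tasks enter no listed variable: 8 + 8 = 16, and 16/44 = 36%. That is not an error in itself, but they could serve as a speed reference.

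**4. Uniform speed change.** Let C and I be a child's mean correct-answer reaction times on congruent and incongruent tasks. The interference cost is I − C. If every response is faster by d, the cost becomes (I − d) − (C − d) = I − C.

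| d (assumed) | Shift in C | Shift in I | Shift in I − C |
|---|---|---|---|
| 25 ms | 25 ms | 25 ms | 0 |
| 50 ms | 50 ms | 50 ms | 0 |
| 100 ms | 100 ms | 100 ms | 0 |

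The documents give no value for d. The last column is zero for any choice.

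**5. Price of the contrast.** For one child on one occasion, take an assumed accuracy p that is equal on both stimulus types, with independent tasks. The standard error in percentage points is 100·√(p(1−p)/12) for congruent tasks, 100·√(p(1−p)/16) for incongruent tasks, and 100·√(p(1−p)(1/12 + 1/16)) for their difference.

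| p (assumed) | Congruent | Incongruent | Difference |
|---|---|---|---|
| 0.70 | 13.2 | 11.5 | 17.5 |
| 0.80 | 11.5 | 10.0 | 15.3 |
| 0.90 | 8.7 | 7.5 | 11.5 |
| 0.95 | 6.3 | 5.4 | 8.3 |

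At p = 0.90 the difference is 11.5/8.7 = 1.3 times as noisy as the congruent score and 11.5/7.5 = 1.5 times as noisy as the incongruent score.

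**The case against.** The strongest reply is that inhibition is not lost. Congruent and incongruent results are kept apart, so anyone can subtract them, and in the 50 ms example a reader would see both variables move together. This stands in part: the information is there. But the subtraction is not a planned result. Two separately reported arm effects do not give an interval for their difference, which depends on the correlation between the two measures within a child.

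Second, the Discussion's specific promise concerns focus and distraction, which congruent and incongruent tasks do address. BRIEF adds parent ratings with Inhibit, Shift and Working Memory scales. Both points are fair. A reader might infer that the executive-function outcome cannot support any conclusion; the documents do not support that. BRIEF does not, however, make good what is claimed for the Flanker task itself.

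Third, a reader might infer that the equal split of 44 tasks is impossible. It is not. The Fig. 2 caption speaks of "standard flanker (target stimulus: middle fish) and reverse flanker (target stimulus: ‘non-middle’ fish) conditions respectively", and the mixed condition holds only those two task types, so a two-way split is a natural reading and fits all the counts. What remains is ambiguous use of one word.

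Fourth, reverse minus standard is not an obvious measure of flexibility. The child first "made two familiarization rounds with blue and pink fish to ensure understanding of the task", after which comes the 45-task test, so the scored tasks may well be the intermingled ones, though the text does not say so. If they are, reverse minus standard may reflect how hard the rule is, and a switching measure would compare switch with repeat tasks. This stands, and it is why no particular flexibility contrast is recommended here.

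Last, a condensed article may leave further derived scores to a fuller document. That limits the weight of the point but does not remove it, because the article itself sets an explicit list beside an explicit claim.

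**Conclusion.** The point holds in limited form. None of the four listed variables is a separate measure of flexibility or working memory, and none is the contrast that tells inhibition from general speed or accuracy. A uniform speed change of any size would appear in full in both reaction-time variables and not at all in interference cost. The claim made for the task is therefore broader than the variables listed for it.

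This rests on taking the article's list as the planned Flanker outcomes; the order of the scored tasks is not stated. The reaction-time shifts and accuracies used above are assumptions.

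The two-or-three-conditions question is a matter of wording and is no evidence that the outcome is invalid. Overall this is a cheap improvement of low severity. It affects a secondary outcome only and leaves the primary math analysis as it is.

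**What to change.** 1. Keep the four variables. Add the between-arm difference in interference cost (the arm-by-congruency term), for accuracy and for correct-answer reaction time, and rest any Flanker statement about inhibition on it. Modelling both stimulus types jointly gives the interval directly.
2. Make no Flanker-based claim about flexibility or working memory unless a rule contrast or a switch-versus-repeat contrast is added that suits the actual task order. Otherwise narrow the wording in the Flanker test section and the Discussion.
3. State whether the 44 tasks are 22 standard and 22 reverse, or are spread over the three described conditions, and whether the scored tasks were intermingled.

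The cost is a few derived variables from responses already recorded and some edited sentences. The downside is wider intervals for the contrast, since it rests on 12 congruent and 16 incongruent tasks per child.
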